### TCLT protocol

Participants will be submitted to TCLT at a 627-nm wavelength, with 0.2-W LED power, 70-mW/cm^2^ power density, 10-J/cm^2^ energy density, 13-mm spot size, and 40 J/cm^2^ per treatment. These parameters were chosen based on the optimal wavelength penetration within biological tissues (wavelength range of 600–1000 nm). At short wavelengths, absorption occurs predominantly by chromophores such as melanin and hemoglobin.

In order to avoid skin burning, the power density of 70 mW/cm^2^ was considered safe. The wavelength (approx. 627 nm) is characterized by a relatively low energy density (40 J/cm^2^) for therapeutic uses. The application of LED irradiation will be in four points in the frontal and parietal regions for 30 s at each point (120 s total/session) three times per week during 6 weeks. The flow chart in Fig. 2 explains the protocol steps.

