**Methods/design:**

This is a double-blinded, randomized, controlled trial of patients with diffuse axonal injury (DAI) due to a severe TBI in an acute stage (less than 8 h). Thirty two patients will be randomized to active coil helmet and inactive coil (sham) groups in a 1:1 ratio. The protocol includes 18 sessions of transcranial LED stimulation (627 nm, 70 mW/cm^2^, 10 J/cm^2^) at four points of the frontal and parietal regions for 30 s each, totaling 120 s, three times per week for 6 weeks, lasting 30 min. Patients will be evaluated with the Glasgow Outcome Scale Extended (GOSE) before stimulation and 1, 3, and 6 months after the first stimulation. The study hypotheses are as follows: (1) transcranial LED therapy (TCLT) will improve the cognitive function of DAI patients and (2) TCLT will promote beneficial hemodynamic changes in cerebral circulation.

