**Fig. 2 Fig2:**
[figure not shown]
Study protocol flow diagram. Thirty patients who meet the inclusion and exclusion criteria will be recruited from the Emergency Department of University of São Paulo General Hospital. After baseline data collection, GOSE evaluation, transcranial Doppler hemodynamic measures, and CT scan, these patients will be randomized at a 1:1 ratio: active coil group vs sham coil group. They will be submitted to 18 sessions of TCLT three times per week and reevaluated with the aforementioned instruments after 1, 3, and 6 months after trauma

During the TCLT sessions, patients will remain seated in bed with head support and with their eyes protected. Eighteen sessions will be carried out, with a total of 56 applications. The same qualified previously trained therapist will perform all TCLT sessions at the same time of the day.

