## Discussion

This study protocol is designed to focus on investigating the neuromodulation role of transcranial LED therapy (TCLT) for patients who are victims of severe traumatic brain injury (TBI) with diffuse axonal injury. The objective of the study is to verify the hypothesis that this therapy presents pro-cognitive effects for rehabilitation.

Different studies have emerged to prove the positive effect of TCTL for neuropsychological diseases. After these results, some studies, most of which are case series [66–68], have approached the effects of this treatment for TBI with interesting results.

No specific clinical trials on intervention in the acute stage of TBI were found, which justifies the need for an investigation of the efficacy and effectiveness of TCLT. Considering the global impact of TBI on public health policies, the idea of a non-invasive therapy which helps in neurorehabilitation has an interesting appeal.

The first animal model described with TBI treated with TCLT (808-nm NIR/red LED) was performed with mice. Mice were submitted to only one TCLT section for 4 h. An important reduction (about 90%) of post-injury area size was noticed. Neurological severity scores were also significantly lower at 28 days for laser-treated mice [66]. A different approach with a 6-min daily TCLT session for 10 days reverted deficits in working memory tests of mice [67].

A two-case study with TCLT performed to improve cognitive function in chronic mild TBI patients found improvements in verbal learning, executive function, and memory [68]. With a higher number of patients with chronic mild TBI, the same author published positive results for 11 patients submitted to 18 outpatient sessions, starting at 10 months to 8 years post-TBI. In this study, each LED cluster head (5.35-cm diameter, 500 mW, 22.2 mW/cm^2^) was applied for 10 min to each 11 scalp placement (13 J/cm^2^). They evidenced improvements in executive function as well as sleep and fewer post-traumatic stress disorders [69].

Increasing the number of sessions, another series of two patients submitted to 18 red/NIR TCLT treatments (500 mW, 22.2 mW/cm^2^, 22.48 cm^2^ per treatment area) in chronic TBI patients (who began TCLT at 10 months to 8 years post-TBI) showed improvements in cognition (mainly executive function and verbal memory) [68].

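### The stated LED dose does not follow from the stated irradiance and time: 70 mW/cm² for 30 s gives 2.1 J/cm² per point, not 10

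*Protocol article*

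**What the plan says.** The TCLT protocol section gives the wavelength as 627 nm and the LED power as 0.2 W, followed by "70-mW/cm^2^ power density, 10-J/cm^2^ energy density, 13-mm spot size, and 40 J/cm^2^ per treatment". Light is applied "in four points in the frontal and parietal regions for 30 s at each point (120 s total/session"), three times a week for 6 weeks. The same section says of the wavelength that it "is characterized by a relatively low energy density (40 J/cm^2^) for therapeutic uses", and of heating: "In order to avoid skin burning, the power density of 70 mW/cm^2^ was considered safe".

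The abstract repeats the key settings: "transcranial LED stimulation (627 nm, 70 mW/cm^2^, 10 J/cm^2^) at four points of the frontal and parietal regions for 30 s each", with 120 s in total, "three times per week for 6 weeks, lasting 30 min".

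The text under Fig. 2 adds: "Eighteen sessions will be carried out, with a total of 56 applications".

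The Background section on the principles of photobiomodulation gives 4 J/cm² as the minimum energy density for the optimal intervention.

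**The concern.** Irradiance, exposure time and fluence are tied by one formula, so any two fix the third. The article states all three, in both the abstract and the TCLT protocol section, and they cannot all be true. Because the same set of figures appears twice, a single slip of the pen is an unlikely explanation.

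Three things are at stake.

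- **The reported dose.** This is the only experimental intervention. A reader trying to replicate it cannot tell whether to deliver 2.1 or 10 J/cm² per point.
- **The dose rationale.** The stated 10 J/cm² is above the article's own 4 J/cm² minimum, while 2.1 J/cm² is about half of it. A null result would be read differently in the two cases.
- **The safety statement.** The assurance about skin burning is made for 70 mW/cm². If the device really delivered 10 J/cm² in 30 s, its irradiance would have to be well above that.

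**Working it through.** **Inputs** (TCLT protocol section unless noted): irradiance 70 mW/cm² = 0.070 W/cm²; 30 s per point; 4 points; 120 s per session; 18 sessions (abstract); LED power 0.2 W; spot size 13 mm; stated fluence 10 and 40 J/cm².

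**Formula.** Fluence (J/cm²) = irradiance (W/cm²) × time (s).

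**Check that the article uses this definition.** In the Discussion, an earlier study's cluster head at 22.2 mW/cm² "was applied for 10 min to each 11 scalp placement (13 J/cm^2"). By the formula, 0.0222 × 600 = 13.3 J/cm², which agrees.

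**The stated figures.**
- Since 4 × 10 = 40, the article's 10 J/cm² reads as the dose per point and 40 as the sum over four points.
- Per point: 0.070 × 30 = 2.1 J/cm², against 10.
- Summed over four points: 2.1 × 4 = 8.4 J/cm², against 40.
- Ratio: 10/2.1 = 40/8.4 = 4.76. The 40 carries the same discrepancy as the 10 and is not a second one.
- Per point over the course: 2.1 × 18 = 37.8 J/cm², against 10 × 18 = 180.

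**What would make 10 J/cm² true.**
- At 70 mW/cm²: 10/0.070 = 142.9 s per point; × 4 = 571 s, or 9.5 min per session, against the stated 120 s.
- At 30 s: 10/30 = 0.333 W/cm² = 333 mW/cm², against the stated 70.

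**Other readings of the text.**

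| Reading | Result (J/cm²) | Why it fails |
|---|---|---|
| 10 is the session total | 0.070 × 120 = 8.4 | Not 10, and leaves 40 unexplained |
| 30 min is irradiation time shared by four points | 0.070 × 450 = 31.5 per point | Matches neither figure and contradicts 120 s |
| 30 min is irradiation time at each point | 0.070 × 1800 = 126 per point | As above |
| 40 is the whole 18-session course at one point | 37.8 | Near 40, but leaves 10 unexplained; the Discussion uses the word treatments for single sessions |
| 0.2 W over a 13-mm diameter spot | Area π × 0.65² = 1.327 cm²; 0.2/1.327 = 151 mW/cm²; × 30 s = 4.5 per point, 18.1 over four | Short by 10/4.52 = 2.2, and contradicts 70 mW/cm² |
| 0.2 W over a 13-mm square | 118 mW/cm²; 3.55 per point, 14.2 over four | Short by 2.8 |
| 0.2 W, 13 mm as radius | 37.7 mW/cm²; 1.13 per point, 4.5 over four | Short by 8.8 |

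No reading yields both 10 and 40. The power and spot-size rows show a further conflict: 0.2 W at 70 mW/cm² needs 0.2/0.070 = 2.86 cm², a circle about 19 mm across rather than 13.

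**Number of applications.** 18 sessions × 4 points = 72, not 56; 56/18 = 3.11 is not a whole number.

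**The case against.** The best counter-argument is about weight. Patients receive a given helmet for a stated time on a stated schedule, and the arms, endpoint, test and sample size make no use of the fluence. The comparison with sham is therefore valid whatever the dose label says. This stands, and it limits the point to reporting, replication and interpretation.

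The factor of 4.8 also depends on 70 mW/cm² being correct, and the LED power and spot size in the same sentence suggest it may not be. This stands too: with 13 mm read as a diameter, the discrepancy is 2.2-fold. The stated doses are still not recovered, and the conflict gives another reason to measure the device.

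On safety, 333 mW/cm² is stated nowhere and would arise only if 10 J/cm² were delivered in 30 s. The Tolerability and safety section reports that the device has been judged safe with regard to heat, and it provides for skin-temperature monitoring and for interrupting a session. No excess exposure is shown, so the safety aspect is a request for confirmation.

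Finally, simply restating 2.1 J/cm² would put the trial below the article's own 4 J/cm² minimum. That is true. It does not make the present figures right, but it does mean that the investigators should address the minimum openly when they correct the dose.

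That the article condenses a fuller protocol does not help here: the figures are present and contradict one another.

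**Conclusion.** The concern holds and should be fixed. As written, the per-point dose is 10 J/cm² by label and 2.1 J/cm² by irradiance and time, a factor of about 4.8. The four-point sum is 40 against 8.4. This assumes continuous emission at the stated 70 mW/cm² for the stated 30 s; the article describes no pulsing, duty cycle or overlapping sources. If 0.2 W over a 13-mm diameter spot is right instead, the dose is 4.5 J/cm² and the factor 2.2. Across these two routes the delivered dose falls on either side of the 4 J/cm² minimum, so the error matters for the dose rationale.

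The document does not show whether irradiance, time or fluence is wrong. The validity of the randomised comparison is not in question. The 56 against 72 applications is a minor, separate slip that does not change what is delivered.

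**What to change.** 1. Measure the helmet's irradiance at the scalp and reconcile it with the stated LED power, spot size and 70 mW/cm².
2. Because recruitment has begun (Trial status), the preferred course is to keep 30 s per point and restate the fluence per point as measured irradiance × 30 s. That is 2.1 J/cm² if 70 mW/cm² is confirmed. Give the dose per point and drop the sum over four different sites.
3. State how the corrected dose stands against the 4 J/cm² minimum in the Background.
4. Only if 10 J/cm² per point was really intended, amend the exposure to about 143 s per point at 70 mW/cm². Record which patients had which dose, since the active arm would then mix two doses.
5. Confirm that the skin-safety statement refers to the measured irradiance.
6. Say whether the 30 min in the abstract is the length of a session. Change 56 applications to 72, or define what an application is.

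Which figure is right is for the investigators and the device engineer to decide.

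**Cost.** The preferred course needs a check of device output and an edit of figures, with no extra patients. Lengthening exposure would add 571 − 120 = 451 s, about 7.5 min of irradiation per session. This may fit within the 30 min if that is the session length, but it requires an amendment during recruitment.

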**Fig. 2 Fig2:**
[figure not shown]
Study protocol flow diagram. Thirty patients who meet the inclusion and exclusion criteria will be recruited from the Emergency Department of University of São Paulo General Hospital. After baseline data collection, GOSE evaluation, transcranial Doppler hemodynamic measures, and CT scan, these patients will be randomized at a 1:1 ratio: active coil group vs sham coil group. They will be submitted to 18 sessions of TCLT three times per week and reevaluated with the aforementioned instruments after 1, 3, and 6 months after trauma

During the TCLT sessions, patients will remain seated in bed with head support and with their eyes protected. Eighteen sessions will be carried out, with a total of 56 applications. The same qualified previously trained therapist will perform all TCLT sessions at the same time of the day.

### Tolerability and safety

All patients will be evaluated after each session. If a major side effect is noticed, medical assistance will be provided for the patient and further examination will be done as necessary. This fact will be written down and discussed to avoid future occurrences. Depending on the case, exclusion of the patient will be considered.

There are no studies with photobiomodulation (PBM) for severe TBI patients in the acute stage of trauma. Considering that fact, some safety precautions will be taken. There are no papers studying the possible effect of increasing the ICP due to PBM. But some chronic-stage studies [52] noticed a blood flow increase. The possible ICP increase due to that will be monitored by ICP catheter insertion or non-invasive methods (when catheter insertion cannot be performed for any reason). Because of the improvement effect in chronic TBI patients, the authors do not believe that this intervention could be harmful. ICP monitoring will add safety to this study. If elevation of ICP happens, the authors will stop the session and observe if intervention for ICP control is required. The patient will be evaluated in the following session, and if elevation happens again, the patient will be excluded.

Another concern would be a possible deleterious effect produced by the heat generated by the helmet in acute-stage TBI patients. Some studies showed an insignificant cortical temperature increase [52, 53]. Our device has already been considered safe in this regard; in addition, the protocol includes monitoring the head skin and global temperature of the patient during the sessions. If there is harmful elevation of skin temperature in the area of stimulation, the session will be interrupted and the patient will be reevaluated. If this effect is noticed in the following session, exclusion of the patient will be considered for safety.

Low-level light therapy (photobiomodulation), which is the principle of therapy of this protocol, is registered on the Food and Drug Administration, and the adverse effects described are ocular injuries and electrical shock [54]. Ocular injuries should not happen in this protocol since the LED will not be applied close to the eyes. But, for safety, the eyes will be evaluated for redness or irritation after each session. Electrical shock is unlikely in this protocol because the helmets are supplied by internal batteries. However, it will be reported and dealt with by the engineer responsible for maintenance of the helmet, if it happens.

### Instruments of evaluation

#### Glasgow Outcome Scale Extended

It is an expansion [55] with the objective of complementing the limitation of the original Glasgow Outcome Scale [56]. Despite being more practical, the five original groups (Dead, Vegetative State, Severe Disability, Moderate Disability, Good Recovery) of the original scale are broad and therefore insensitive to subtle changes in functional status [55]. The 8-point Glasgow Outcome Scale Extended (GOSE), developed only in 1981, provides different criteria to subdivide the upper three categories of the scale: Death, Vegetative State, Lower Severe Disability, Upper Severe Disability, Lower Moderate Disability, Upper Moderate Disability, Lower Good Recovery, Upper Good Recovery [57].

#### Adams grading scale for diffuse axonal injury

In 1989, this classification was first published grading diffuse axonal injury [58]:Grade 1: histological evidence of axonal injury in the white matter of the cerebral hemispheres, the corpus callosum, the brain stem, and, less usually, the cerebellum.Grade 2: there is also a focal lesion in the corpus callosum.Grade 3: there is, in addition, a focal lesion in the dorsolateral quadrant or quadrants of the rostral brain stem.

In the present study, the principles of the histological Adams grading scale will be applied on the MRI scans of the patients.

#### Marshall computed tomographic classification

The first Marshall classification based on computed tomographic abnormalities was published in 1991 [59] and was composed of four groups of patients. In 2005, these criteria were reviewed and two new groups were added [60]. Recently, the Marshall computed tomographic classification has six different groups:Diffuse injury I (no visible pathology)—no visible intracranial pathology seen on the CT scan.Diffuse injury II—cisterns are present with a midline shift of 0–5 mm and/or lesion densities present; no high- or mixed-density lesion 25 cm^3^; may include bone fragments and foreign bodies.Diffuse injury III (swelling)—cisterns compressed or absent with a midline shift of 0–5 mm; no high- or mixed-density lesion 25 mm.Diffuse injury IV (shift)—a midline shift of 5 mm; no high- or mixed-density lesion 25 cm^3^.Evacuated mass lesion V—any lesion surgically evacuated.Non-evacuated mass lesion VI—high- or mixed-density lesion 25 cm^3^; not surgically evacuated.

#### Gennarelli’s clinical classification

This is a classification of the severity of DAI with three levels: in mild DAI, coma lasts 6–24 h. In moderate DAI, coma lasts longer than 24 h but there is no abnormal posturing. In severe cases of DAI, the coma duration is longer than 24 h and signs of brain stem impairment (decortication or decerebration) can also be found [44].

#### Abbreviated Injury Scale

It is an anatomically based scale created in a global consensus for scoring the severity of trauma. It is a 6-point ordinal scale: (1) minor, (2) moderate, (3) serious, (4) severe, (5) critical, (6) maximal (currently untreatable) [47].

### Cerebral blood flow evaluation

#### Transcranial Doppler

All patients will be evaluated by transcranial Doppler before the first stimulation and after the last one. Evaluation will be done by a doctor expert in transcranial Doppler who will not be aware of the patient’s group (intervention vs sham). The transcranial Doppler parameters of evaluation include the following: blood flow velocities (systolic and diastolic) of the bilateral middle cerebral arteries as well as the basilar artery. The device that will be used for measuring is a transcranial Doppler ultrasound (LOGIQ; GE Healthcare Systems, Wauwatosa, WI, USA, 2012) with a 2-MHz transducer. The mean flow velocity (cm/s) will be obtained every second (sampling rate of 1 Hz) and saved for analysis. The three best measures of the systolic velocity, diastolic velocity, pulsatility index, and resistance index will be selected to calculate the mean values [52].

Evaluation with the transcranial Doppler will be performed by one expert doctor only to maintain a uniform measurement of TBI patients.

### Outcome variables

#### Primary

Improvement in functional outcome measured by the GOSE after 3 months of the first stimulation [57].

The authors decided for an approach based on dichotomizing the GOSE (favorable vs unfavorable response). For analysis of outcomes at 3 months, the authors pre-specified death, persistent vegetative state, and severe disability on the GOSE as unfavorable outcomes. Analyzing the GOSE on a binary outcome measure reflects success or failure more plainly, which simplifies the matter of assigning a score to a patient too cognitively impaired to be tested. Moreover, describing the study on this way eases the interpretation for clinical significance [61]. Many studies in TBI [61–63] analyze and prefer to interpret this scale in its dichotomized form.

#### Secondary

Improvement in early and delayed functional outcomes measured by the GOSE after 1 and 6 months of the first stimulation.Improvement effects of TCLT in follow-up images measured by the Marshall computed tomography scale [60], the Adams grading scale [58], and Gennarelli’s clinical severity scale [44] for diffuse axonal injury.Hemodynamic improvement effect of TCLT measured by transcranial Doppler (systolic and diastolic velocities of the middle cerebral (MCA) and basilar arteries (BA) and the pulsatility index and resistance index values) [44]. It will be evaluated before stimulation and 1, 3, and 6 months after the first stimulation.

For GOSE 1 and 6 months after the first stimulation, a similar calculation of the primary variable outcome will be used.

Patients will repeat the CT scan and the MRI after 1 month of treatment, and they will be evaluated again for the following scales: Gennarelli’s, Adams’, and Marshall’s, and a comparison with image findings of the sham group will be performed.

The transcranial Doppler will analyze systolic and diastolic velocities of the MCAs and BAs and pulsatility index and resistance index values. The means and standard deviation will be calculated for these variables and compared with the first evaluation before stimulation.

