### Severe TBI evaluation and management at University of São Paulo General Hospital

At University of São Paulo General Hospital, all severe TBI patients are managed in an intensive care unit. An ICP monitoring catheter is inserted in patients who present with the criteria for ICP monitoring [50]:

GCS ≤8 and:▪ Marshall ≥2 head CT scan or▪ Normal head CT scan and at least two of the following three criteria:PAS ≤90 mmHgAge >40Pathological posture (decerebration or decortication)

The decision for catheter insertion is made by the on-call attending neurosurgeon. Patients in whom the catheter cannot be inserted for any reason are evaluated by non-invasive strategies (optic nerve sheath ultrasonography or transcranial Doppler) for ICP monitoring and CT scan. In our center, all TBI patients are submitted to head CT scans at admission, within 6 h after trauma, on the third and the fifth day after trauma, or before these times if they present any neurological deterioration (which is commonly defined as a decrease of two or more points in the motor component of the Glasgow Coma Scale) [51]. When patients need to be hospitalized for longer than 5 days, the decision for the following head CT scans is individualized. All TBI patients in coma are evaluated with electroencephalogram (EEG) for seizure diagnosis in the intensive care unit (ICU).

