### Statistical analysis

The primary outcome variable will be analyzed with chi-square for comparison of dichotomized GOSE (favorable vs unfavorable) between intervention and sham. The second outcome measures for GOSE at 1 and 6 months after stimulation will be calculated in the same way as for the primary outcome measures. The results of the scales of DAI severity (Gennarelli’s), Adams, and Marshall will be compared with the results of the sham group with the Mann-Whitney *U* test. The second outcome measures related to hemodynamic evaluation will be analyzed with the *t* test for means and SD comparison of 1, 3, and 6 months with the basal value before stimulation.

The median and interquartile range will be calculated for age, intensive care unit days, hospitalization days, and days of treatment of infection. Gender, handedness, level of schooling, mechanism of injury, type of accident, sedation, pupils and presence of dysautonomia, presence of infection, and site of infection will be presented as absolute frequency, proportion, and confidence interval. The Glasgow Coma Scale score will be divided into four categories (3–5, 6–8, 9–12, 13–15) and will be expressed as absolute frequency, proportion, and confidence interval at four moments (scene, admission, discharged from ICU, and discharge from hospital).

Statistical Package for the Social Sciences software version 23.0 for Windows (Prentice Hall, Chicago, IL, USA) will be used for analyzing data. A significance level of *p* < 0.05 will be considered for data analysis.

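### Gennarelli's class describes the acute coma and cannot be re-graded on 1-month imaging; the Marshall comparison beside it is truncated, not void

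*Protocol article*

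**What the plan says.** All references are to the protocol article.

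- **Outcome variables, Secondary.** The imaging outcome opens with "Improvement effects of TCLT in follow-up images measured by the Marshall computed tomography scale" and goes on to name the Adams grade and Gennarelli's scale. Timing: "Patients will repeat the CT scan and the MRI after 1 month of treatment, and they will be evaluated again for the following scales". The three scales are then set against the image findings of the sham group.
- **Secondary outcome measures** (under Study purpose and objectives). The same imaging outcome is described with Marshall and Adams only; Gennarelli is absent.
- **Gennarelli's clinical classification.** The lower classes: "in mild DAI, coma lasts 6–24 h. In moderate DAI, coma lasts longer than 24 h but there is no abnormal posturing". The severe class: "the coma duration is longer than 24 h and signs of brain stem impairment (decortication or decerebration) can also be found".
- **Statistical analysis.** The three scales "will be compared with the results of the sham group with the Mann-Whitney" U test. No baseline grade enters. In the same paragraph the Doppler outcomes are compared with their pre-stimulation value.
- **Sampling.** Entry requires coma of more than 6 h and Marshall I or II. New surgical lesions or signs of intracranial hypertension on follow-up CT are listed as an exclusion.
- **Severe TBI evaluation and management.** After the early scans, routine CT is repeated "on the third and the fifth day after trauma, or before these times if they present any neurological deterioration".
- **Tolerability and safety.** On ICP elevation during sessions: "if elevation happens again, the patient will be excluded".
- **Fig. 2 legend.** CT is among the assessments made before randomization; MRI is not named there.

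**The concern.** The outcome conflicts with the article's own definition of the scale. Gennarelli's class records what happened in the acute coma. It is not read from a scan, and its coma component cannot improve. If it is tested between arms under the label of improvement, a chance imbalance in injury severity could be reported as an effect of the LED therapy.

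Marshall raises a different and milder question. Patients enter only in the two lowest classes, and some deterioration is grounds for exclusion. If randomized patients are dropped from the analysis for that reason, the comparison loses the worsening it should record. The loss could differ by arm, because Tolerability and safety itself names a treatment-related rise in ICP as a possibility.

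**Working it through.** The plan gives no figure for these outcomes, so there is none to reproduce. The inputs taken from it are 16 patients per arm and alpha 5% (Sample size calculation). Sidedness is not stated; two-sided is assumed.

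**1. Can Gennarelli's class improve?** Let T be coma duration.

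- Mild: T from 6 to 24 h.
- Moderate: T above 24 h, no abnormal posturing.
- Severe: T above 24 h, with decortication or decerebration.

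Entry needs T above 6 h, so every patient is at least mild. T never decreases, so once it passes 24 h mild is closed for good. Neither T nor posturing is an image finding, so the repeat CT and MRI add nothing to the class.

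**2. How much treatment could precede the 24 h cut?** There are 3 × 6 = 18 sessions. None can come before 6 h, because entry requires coma longer than that. Sessions are given at the same time of day (text after Fig. 2), so a second falls no earlier than about 6 + 24 = 30 h. At most 1 of 18 sessions (1/18 = 5.6%) precedes the cut. It may be none, because the hour of the first session is not stated.

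**3. What does the test do when the class is settled before treatment?** Both arms then share one distribution. Tie-corrected Mann-Whitney, 16 per arm, 4,000 simulated trials for each assumed distribution:

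| Mild / moderate / severe, both arms | Rejection rate |
|---|---|
| 30 / 40 / 30% | 4.9% |
| 10 / 30 / 60% | 5.0% |
| 20 / 50 / 30% | 4.9% |

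This is alpha and nothing more. About half, roughly 2.5%, would favour the active arm. If instead a pre-24 h session did shift the acute class, from 20/50/30% to 40/35/25% or to 50/30/20%, the test would reject in 16% or 31% of trials. That would be an effect on the acute coma, not an improvement seen at 1 month.

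**4. What can Marshall still show?** The article separates class I (nothing visible) from class II (lesion densities and/or a shift of up to 5 mm). A move from II to I or from I to II triggers no exclusion by itself. If every higher class were lost, a two-level score would remain. Power of the tie-corrected Mann-Whitney test, 16 per arm, by exact binomial enumeration over assumed shares in class I at 1 month:

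| Sham | Active | Rejection rate |
|---|---|---|
| 30% | 30% | 4.3% |
| 30% | 50% | 20% |
| 30% | 60% | 41% |
| 30% | 70% | 64% |
| 30% | 80% | 85% |
| 10% | 50% | 71% |

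Power is low for modest differences but not absent.

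**5. Is a baseline grade available?** For Marshall, yes: CT precedes randomization. For Adams, not always: Sampling plans MRI for all patients but also accepts the diagnosis without one, and Baseline measures lists no Adams grade.

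**The case against.** **The Marshall outcome is not void.** From the entry limit and the exclusions, a reader might infer that Marshall worsening is removed by design and that the outcome cannot show an effect. The documents do not support this. Moves between I and II stay observable. The follow-up CT criterion stands in the eligibility list, and nothing says that it operates after randomization; if it acts before, it only defines the population. The ICP rule does act during treatment, but the article does not say that such patients leave the analysis. This objection stands, and the Marshall point is conditional for that reason.

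**Gennarelli's class may not be fully fixed at treatment start.** The article sets no time limit for observing posturing, so a moderate versus severe difference could arise after 24 h. A patient could also be randomized before 24 h with the class unsettled. The count of 1 in 18 sessions bears only on the mild cut and is not an effect size. All of this is correct. It means that a difference between arms is pure chance imbalance only where the class was settled beforehand, and that the class is not automatically a safe covariate. It does not make the class an imaging finding or let a patient past 24 h return to mild.

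**Adjustment is a preference.** An unadjusted Mann-Whitney comparison of randomized arms is valid, and covariate detail often sits in an analysis plan. This also stands: adjustment is offered as a cheap gain in efficiency, not as the repair of an error. Strata within 16 per arm would be thin, which favours a regression model over a stratified rank test.

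**Conclusion.** The point holds firmly for Gennarelli's class and conditionally for Marshall.

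For Gennarelli, the listed outcome contradicts the article's definition, and the two descriptions of the imaging outcome disagree on whether the scale belongs there. This needs no outside figure. That its test carries no information about treatment rests on one assumption: that the class is settled before the first session.

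For Marshall, the outcome is truncated and weakly powered for modest differences. The power figures rest on assumed class I shares and on the extreme case in which all higher classes are lost. Bias arises only if either exclusion removes randomized patients from the comparison, which the article leaves open.

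Adams is touched only by the suggestion to adjust. All of this concerns secondary outcomes; the GOSE analysis and the sample size do not depend on it.

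**What to change.** 1. Remove Gennarelli's class from the 1-month imaging outcomes and delete its between-arm test. This also brings the two outcome lists into agreement.
2. Report the class by arm as a descriptor of acute injury severity. Use it as a covariate only if it is determined before randomization.
3. State that randomized patients whose CT worsens, or whose sessions are stopped, stay in the Marshall comparison at their observed class. This concerns the analysis only and leaves the clinical stopping rules as they are. State also whether the follow-up CT criterion applies before or after randomization.
4. Adjust the 1-month Marshall comparison for baseline class, for example by ordinal regression. Do the same for Adams where a baseline MRI grade exists.

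Cost: one secondary outcome is lost, and the outcome and analysis wording changes. No new procedure is needed, beyond obtaining the 1-month CT also in patients who worsened or stopped sessions, if the present plan would have dropped them.
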